### 11.4 IMP Dosage and Administration

Losmapimod 7.5mg BD (twice daily): 1 x 7.5mg tablet each morning and each evening for 16 weeks. Placebo: one Placebo tablet to match Losmapimod each morning and each evening, for 16 weeks

Dispensing of IMP will be on V3, V5, V6 and V7. At the point of initial dispensation, the bottles will contain 70 tablets. Participants will be expected to bring their trial medication in with them every visit.

Participants will be required to swallow each tablet with approximately 240mL of water.

**Table 3:**

| Regimen | Description         |
|---------|---------------------|
| A       | 7.5mg Losmapimod BD |
| P       | Placebo BD          |

#### 11.4.1 Maximum dosage allowed

Participants will receive Losmapimod 7.5mg BD or Placebo BD. This makes 15mg Losmapimod the maximum daily dose allowed in this clinical trial.

#### 11.4.2 Maximum duration of treatment of a participant

The maximum duration of treatment will be 112 days.

#### 11.5 Descriptions: Losmapimod and matching Placebo

Losmapimod tablets (wet granulation formulation) are available as white, film coated, round, bi-convex tablets manufactured using micronised Losmapimod active substance. Tablets are available containing 7.5 mg of Losmapimod and are packed into high-density polyethylene (HDPE) bottles .

The placebo product visually matches the GW856553 Tablets 7.5 mg. The film coat used for the placebo product, Opadry white OY-S-28876, is identical to that used for the active tablets. The placebo product is manufactured using commonly used and recognised tablet excipients that are also employed in the active tablets and are packed into high-density polyethylene (HDPE) bottles.

The complete statement of the components and quantitative composition of Placebo to Match GW856553 Tablets is given in Table 4.

**Table 4: Composition of Placebo to Match GW856553 Tablets**

| Component                        | Theoretical Unit Quantity (mg/tablet) | Function         | Reference to Standard |
|----------------------------------|---------------------------------------|------------------|-----------------------|
| Lactose Monohydrate              | 79.88                                 | Diluent          | Ph.Eur. or USP/NF     |
| Microcrystalline Cellulose       | 60.0                                  | Diluent          | Ph.Eur. or USP/NF     |
| Sodium Starch Glycolate          | 9.0                                   | Disintegrant     | Ph.Eur. or USP/NF     |
| Magnesium Stearate               | 1.13                                  | Lubricant        | Ph.Eur. or USP/NF     |
| Core Tablet Weight        | 150.0                          | -                | -                     |
| Opadry White OY-S-28876(1,2)     | 4.5                                   | Film coat        | Supplier              |
| Purified Water(3)                | qs                                    | Suspending Fluid | Ph.Eur. or USP        |
| Film Coated Tablet Weight | 154.5                          | -                | -                     |

**Notes:**

1. The film coat contains the polymer hypromellose Ph.Eur (E464), the colourant titanium dioxide Ph.Eur. (E171) and the plasticizer Macrogol 400 Ph.Eur.
2. Opadry white OY-S-28876 is prepared typically as a 12-13% w/w aqueous suspension. The weight of film coat applied per tablet may vary depending upon the efficiency of the process but is typically 3 % of the tablet core weight.
3. Removed during processing. Does not appear in final product ..

#### 11.5.1 Specification for placebo tablets

Clinical trial batches for placebo tablets will meet the following specification at release and throughout the shelf-life.

**Table 5: Specification of Placebo to match GW856553 tablets**

| Test        | Acceptance Criteria                               |
|-------------|---------------------------------------------------|
| Description | White, round, biconvex, plain, film coated tablet |

|                                      |                                                                          |
|--------------------------------------|--------------------------------------------------------------------------|
| Absence of GW856553X by HPLC1 | Not detected by HPLC analysis (less than 0.1% with respect to GW856553X) |
|--------------------------------------|--------------------------------------------------------------------------|

**Notes:**

1. All placebo batches will comply with the test for absence of GW856553X if tested. When batches are manufactured in the same facility as the active material, the above test is performed using the method described in the IMPD for GW856553 Tablets. Where generic placebo batches to match multiple active products are made in facilities where the active products are not produced, absence of active is assured through the application of GMP and by review of batch records.

### **11.6 Losmapimod drug interactions**

There are no clinically significant interactions with other drugs. Special precautions with BCRP substrates with a narrow therapeutic index (daunorubicin, doxorubicin, topotecan, mitoxantrone) are advised (Section 11.2.3), therefore patients on these drugs will not be permitted to participate in the trial, nor are these medications permitted during the trial. Please refer to the latest version of the IB for more information.

### **11.7 Handling and Storage of IMP**

GSK will be providing the IMP for free of charge for the use in this trial. For further details of finished product processes and distribution to Cambridge University Hospitals NHS Foundation Trust and Royal Brompton & Harefield Foundation NHS Trust, refer to the pharmacy section of the TPM.

The IMP must be dispensed and administered according to procedures described in the TPM pharmacy section. Only participants enrolled in the trial may receive the IMP, in accordance with all applicable regulatory requirements. Only authorized site staff may supply or administer IMP. All IMP must be stored in a secure area with access limited to the investigator and authorized site staff and under physical conditions that are consistent with IMP-specific requirements.

IMP must be stored at room temperature up to 30°C (86°F). The expiry date is stated on the product label, for each package of IMP.

### **11.8 IMP Accountability**

The investigator and institution, is responsible for IMP accountability, reconciliation, and record maintenance. In accordance with all applicable regulatory requirements, the investigator, or designated site staff (e.g., pharmacist or pharmacy staff, where applicable) must maintain IMP accountability records throughout the course of the trial. The responsible person(s) will document the amount of IMP received, the amount supplied and/or administered to and returned by patients. The responsible person(s) in pharmacy will destroy any returned drug once permission from the sponsor has been received.

### **11.9 Treatment Assignment**

Participants will be randomised to the Losmapimod or Placebo regimen in a 1:1 ratio. The randomisation will be stratified by treatment centre. A delegated member of the trial team will log into the website <https://prod.tenalea.net/cctu/DM/default.aspx> using a secure password. They will enter the following information

- Subject Number
- Subject Initials
- Subject DoB
- Confirmation of eligibility
- Inc/Exclusion criteria confirmation

The system will provide a box number which will be used by the site pharmacy to provide the treatment allocated in a double-blinded manner.

### **11.10 Treatment Compliance**

When participants are dosed at the trial site, they will receive IMP directly from an appropriately trained and delegated member of the clinical research team. The date and time of each dose administered in the clinic will be recorded in the source documents. The dose of IMP will be confirmed prior to dosing by a member of the trial site staff other than the person administering the IMP. A member of the clinical research team will examine each patient's mouth to ensure that the IMP was swallowed.

Participants will be required to bring back their trial medication bottles to each treatment visit. Participants remaining medication will be then counted to confirm compliance.

### **11.11 Concomitant Medications and Non-Drug Therapies**

All concomitant medications will be recorded in the eCRF.

Participants taking systemic steroids (IV or Oral) within 4 weeks of the final treatment visit (V9) will be excluded from the primary analysis.

### **11.12 Treatment after EVOLUTION Trial**

There will be no treatment with Losmapimod after the end of the trial. Participants enrolled into this trial will already be receiving the appropriate standard of care, and this care will be continued at the end of the trial.

### **11.13 Treatment of IMP Overdose**

Any signs or symptoms of overdose will be treated symptomatically. No specific antidote is known and the investigator will use clinical judgment. Participants that have taken an overdose of IMP will be withdrawn from the trial.

### **11.14 Legal status of the drug**

Losmapimod is an unlicensed investigational medicinal product currently in development by GlaxoSmithKline (GSK) for the treatment of cardiovascular disease and chronic obstructive pulmonary disease (COPD). Losmapimod has also been evaluated in patients with rheumatoid arthritis, major depressive disorder and neuropathic pain syndromes but these indications are no longer being investigated.

The trial is being carried out under a Clinical Trial Authorisation. The drug is therefore only to be used by the named investigators, for the participants specified in this protocol, and within the trial.

## **12 Procedures and Trial Assessments**

Trial assessments and procedures will be performed by suitably qualified and delegated trial personnel as described in the TPM. Informed consent must be obtained from the participant prior to any trial-specific procedures taking place.

### **12.1 Trial Visits**

The following sections describe in detail the procedures and investigations participants will be subjected to. Further details are available in the Trial Procedures Manual and the electronic Case Report Forms (eCRFs).

#### **12.1.1 Timing of assessments**

Please refer to Table 7 page 55 for timings of assessments

### **12.1.2 Screening, V1 (Day -45 to Day -14)**

Participants will attend the unit for a screening visit within 45 days prior to administration of the first dose of trial medication (V3). Written informed consent must be obtained prior to performance of any protocol specific procedures. The following procedures will be performed:

- Medical history including smoking history.
- Current medication history prior to the screening visit.
- Demography (date of birth, age, gender and race).
- Physical examination including height, weight, BMI, vital signs.
- 12-lead ECG (triplicate).
- Spirometry post bronchodilator.
- Following an overnight fast, blood (approximately 55ml) and urine will be collected for clinical chemistry (including urea, creatinine, uric acid, electrolytes, liver function and glucose and HbA1c if diabetic), Full Blood Count (including haemoglobin, platelets and differential white cell count), HIV, Hepatitis B surface antigen, Hepatitis C antibody, urinalysis.
- Biomarkers.

Participants detailed cardiovascular and respiratory (and other systems) medical history will be collected, including information regarding any known allergies to drugs, use of concomitant medications, detailed history of smoking and alcohol consumption and history of blood donation and/or participation in clinical trials. The 45 day screening period may be extended if patients have an exacerbation that requires steroid or antibiotic use. This period will be extended by at least the equivalent time of steroid use added onto the 45 day period or up to the discretion of the PI where clinical judgement is required. Patients who have failed screening because of changes to trial inclusion/exclusion criteria or did not attend screening due to medical reasons (i.e. an exacerbation) and their medical status has now changed may be rescreened if they are keen to participate in the trial and happy to undergo a repeat screening, at the discretion of the PI and based on clinical judgement.

### **12.1.3 V2 Imaging visit - FDG-PET/CT (Day -14 to Day -1)**

Between Days -14 to -1, participants will undergo a FDG-PET/CT scan. A clinical report without significant incidental findings allows the participant to be randomized into the trial, unless the findings are deemed to not require further investigation at the discretion of the PI, or after subsequent investigation before dosing with Losmapimod. Any significant findings at this visit necessitating withdrawal from the trial will be termed an Adverse Event unrelated to drug as this scan precedes drug administration. Patients who have attended the imaging visit but do not progress within 14 days onto the trial due to the necessity to investigate abnormalities on the PET-CT / MRI scan may be considered for subsequent entry onto the trial without undergoing a repeated imaging visit, if performed within a reasonable timeframe, and at the discretion of the PI and based on clinical judgement.

FDG-PET/CT imaging is expected to last for approximately 2hrs 20 minutes with a 30 minute break.

#### **12.1.5 Treatment Period**

At each visit, procedures/assessments can take place in any order, but dosing should only occur after all assessments have been completed.

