### **9.6 Trial endpoints**

#### **9.6.1 Primary endpoints**

Change in vascular inflammation (using derivatives of Standard Uptake Value (SUV) and Tissue to Background Ratio (TBR) in the carotid and aortic arteries of patients following 16 weeks of treatment.

Change in flow mediated dilatation post-ischaemia and/or flow mediated dilatation post-Glyceryl trinitrate, following 16 weeks treatment.

Change in atheromatous plaque and vessel wall characterisation using MRI and/or FDG-PET/CT, following 16 weeks of treatment. MRI analysis will be dependent on a sufficient number of datasets since this was an optional sub-study (please see section 15 of the protocol for further details).

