#### **V3 (Day 1):**

All assessments at this visit should be completed **prior** to participants receiving IMP.

- Concomitant medication check (confirm no systemic corticosteroids have not been used since V1).
- Vital Signs.
- Blood (55ml in total) and urine collection for clinical chemistry (including lipid profile), haematology, urinalysis.
- Blood collection for biomarkers (inclusive within the 55ml as above).
- 12 Lead ECG (triplicate).
- Adverse event assessment.
- Arterial haemodynamics: arterial stiffness, BP and HR.
- Flow mediated dilatation.
- Spirometry post bronchodilator (FEV1 and FVC).
- SNIP (Sniff Nasal Inspiratory Pressure) measurements.
- 6 minute walk test.
- Randomisation and administration of first dose of IMP, and provision of IMP in participant packs.
- Biomarkers Fibrinogen and hsCRP (inclusive within the 55ml as above).
- Blood collection for serum store (inclusive within the 55ml as above).

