### **V9 (Days 109-112):**

During any of these days (but ideally should take place on Day 112):

- Concomitant medication check.
- Vital Signs.
- Blood (55ml in total) and urine collection for clinical chemistry (including lipid profile), haematology, urinalysis.
- Biomarkers Fibrinogen and hsCRP (inclusive within the 55ml as above).
- Blood collection for serum store (inclusive within the 55ml as above).
- Adverse event assessment.
- Arterial haemodynamics: arterial stiffness, BP and HR.
- Flow mediated dilatation.
- SNIP (Sniff Nasal Inspiratory Pressure) measurements.
- 6 minute walk test.
- 12 Lead ECG (triplicate).
- Spirometry post bronchodilator.
- IMP Compliance check and final medication retrieval.

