### 12.5 Non Imaging End Points

#### 12.5.1 Flow mediated dilatation

Endothelial function will be assessed in the brachial artery of the non-dominant arm using the technique of flow mediated dilatation. Vessel diameter will be measured, using high-resolution vascular ultrasound with a 5-20MHz linear-array transducer, continuously for 1 minute at baseline, and for a further 5 minutes following release of a cuff inflated to 200mmHg, placed distal to the ultrasound probe. After return to baseline, vessel diameter will be measured continuously for 5 minutes following administration of 25µg of sublingual glyceryl trinitrate (GTN). FMD is defined as the maximum percentage increase in vessel diameter during reactive hyperemia; GTN-mediated dilatation is defined as the maximum percentage increase in vessel diameter after sublingual GTN. This is a standard technique.

Additional details on the procedure are provided in the TPM.

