## **12.8 Trial restrictions**

### **12.8.1 Meal and Dietary Restrictions**

Participants will be asked to abstain from ingestion of alcohol and caffeine 12 hours prior to the first dose of trial medication and until collection of the final blood sample at each individual trial visit. Participants will be required to fast overnight prior to each clinical chemistry and haematology blood sample collection. Participants undergoing FDG-PET/CT and  $\pm$  MRI scanning will be required to fast for 6 hours prior to scanning. Previous studies have not identified a major effect of food in the systemic exposure of Losmapimod; therefore, there are no food restrictions other than the ones indicated above.

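### Section 12.1.5 leaves the order of tests at V3 and V9 free, so spirometry after bronchodilator and the walk test may precede FMD, and these or GTN may precede PWV and augmentation index, adding avoidable noise

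*Protocol*

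**What the plan says.** Section 12.1.5 gives one rule for sequence within a visit: "At each visit, procedures/assessments can take place in any order, but dosing should only occur after all assessments have been completed". The V3 entry adds only that "All assessments at this visit should be completed" before the first dose. The V9 entry gives a window of days, "During any of these days (but ideally should take place on Day 112", and no order.

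Both visits list arterial haemodynamics, FMD, spirometry, sniff pressure, the 6-minute walk, a triplicate ECG and bloods. Spirometry follows a bronchodilator at both; the V9 entry reads "Spirometry post bronchodilator".

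Section 9.6.1 makes FMD primary: "Change in flow mediated dilatation post-ischaemia and/or flow mediated dilatation post-Glyceryl trinitrate, following 16 weeks treatment". Section 9.6.2 makes aortic pulse wave velocity (PWV) and augmentation index secondary.

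Three places control conditions for single tests:

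- Section 12.5.1 fixes the order inside the FMD test. The cuff-release recording comes first, and then "After return to baseline, vessel diameter will be measured continuously for 5 minutes following administration of" 25 µg of sublingual GTN. It states no rest period before the test.
- Section 12.5.3 asks for 5 minutes of seated rest before blood pressure and the radial waveform, and 15 minutes of supine rest before PWV.
- Section 12.8.1 restricts caffeine from 12 hours before the first dose and "until collection of the final blood sample at each individual trial visit".

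**The concern.** Some of these tests may act on what others measure. The protocol itself defines the GTN response as an increase in vessel diameter, waits for the vessel to recover before giving GTN, and asks for rest before haemodynamic readings. It therefore recognises carry-over within a test, yet section 12.1.5 sets aside control of carry-over between tests.

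FMD, PWV and augmentation index are analysed as changes from V3 to V9. If a participant has the bronchodilator and the walk before FMD at one visit and after it at the other, the change contains an order effect that has nothing to do with losmapimod. Section 16.4 justifies the sample size by the half-width of the confidence interval and says that a smaller one is desirable, so avoidable variance works against the trial's own aim.

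**Working it through.** **1. Which orders are possible under the text**

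| Earlier test | Later test | Allowed? | Protection in the protocol |
|---|---|---|---|
| Bronchodilator and spirometry | FMD | Yes (12.1.5) | None stated |
| 6-minute walk | FMD | Yes | None stated; 12.5.1 gives no rest |
| Bronchodilator and spirometry | PWV, augmentation index | Yes | No interval tied to the bronchodilator |
| 6-minute walk | PWV, augmentation index | Yes | 5 min seated and 15 min supine rest (12.5.3): partial |
| GTN step of the FMD test | PWV, augmentation index | Yes | No interval tied to GTN |
| GTN | Post-ischaemia FMD | No | 12.5.1 puts GTN after that recording |

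No section requires the order used at V3 to be repeated at V9, or to be the same at the two sites.

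The visit lists cannot be read as a sequence. At V3 spirometry is listed before the walk and at V9 after it. The V3 list also puts fibrinogen and hsCRP sampling below the first dose, although assessments must precede dosing.

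**2. Caffeine**

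At V3 the restriction starts 12 hours before the first dose, and dosing comes after all assessments, so the V3 vascular tests are covered. At V9 it ends with the last blood sample. A participant bled first may have caffeine before FMD and PWV.

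**3. The plan's own figure**

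The only precision figure is in section 16.4: SD 0.3, 30 per arm, 90% chance of a half-width of 0.17 or less. Half-width at the assumed SD = 1.96 × 0.3 × √(2/30) = 0.152. Letting the sample SD vary on 58 degrees of freedom, the 90th percentile is 0.169 and the chance of 0.17 or less is 0.908. With the t critical value these are 0.173 and 0.861. The figure reproduces with the normal value, or with t after rounding. It concerns TBR. The protocol gives no SD for FMD, PWV or augmentation index, and no size for any order effect.

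**4. Illustration under stated assumptions**

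Let d be the shift caused by a disturbing order, in SDs of the change score without order effects. Let p be the probability of that order, independent at each visit. These values are assumptions, not from the protocol.

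- Added variance of the change = 2 × p × (1 − p) × d²
- Half-width multiplier = √(1 + added variance)
- Participants' worth of 60 = 60 / (1 + added variance)

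| p | d | Added variance | Half-width | 60 participants worth |
|---|---|---|---|---|
| 0.5 | 0.5 | 2 × 0.25 × 0.25 = 0.125 | √1.125 = 1.061 | 53 |
| 0.5 | 1 | 2 × 0.25 × 1 = 0.5 | √1.5 = 1.225 | 40 |
| 0.1 | 0.5 | 2 × 0.09 × 0.25 = 0.045 | √1.045 = 1.022 | 57 |
| 0.1 | 1 | 2 × 0.09 × 1 = 0.18 | √1.18 = 1.086 | 51 |
| 0 or 1 | any | 0 | 1.000 | 60 |

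The value p = 0.5 is the worst case, because p(1 − p) is largest there. With a stable order a constant order effect cancels in the change. The calculation treats a simple change score and ignores the baseline covariate of section 16.1, so it is approximate.

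**The case against.** The strongest reply is that the any-order rule is permissive and the detail lies in the Trial Procedures Manual, to which sections 12.1, 12.5.1 and 12.5.3 refer. The manual is not shown and may set a sequence. Sites also tend to form habits, and with a stable order the added variance is close to zero. Section 16.1 places the main focus on PET/CT, done at V2 and V8 and untouched by this rule. The effect of a test dose of bronchodilator in these participants is not given anywhere in the protocol.

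Most of this stands and limits the size of the point. It does not remove it. If the manual fixes an order, section 12.1.5 gives sites leave to depart from it, and the two need reconciling.

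A reader might infer more than the text supports:

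- *That GTN can disturb FMD within a visit.* It cannot. Section 12.5.1 gives GTN after the post-ischaemia recording and after recovery, and the post-GTN reading is the purpose of giving it.
- *That a walk before blood sampling breaks the activity restriction.* Section 12.8.2 bars strenuous activity; section 12.6 describes a self-paced walk with breaks. No clear conflict follows, and nothing in the protocol shows that the biomarkers would shift.
- *That caffeine is uncontrolled before the V3 vascular tests.* The 12-hour rule before the first dose already covers them.
- *That the treatment comparison is biased.* Both arms follow the same rule under double blinding, randomisation is stratified by centre, and the analysis adjusts for centre. A site that changes its order affects both arms. Bias would need the order to differ by arm, and nothing suggests that.

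**Conclusion.** The point holds as a matter of precision and comparability. Section 12.1.5 allows post-bronchodilator spirometry and the walk before FMD, and these or GTN before PWV and augmentation index, with no washout between tests and no requirement for the same order at V3 and V9. The rests in section 12.5.3 only partly address the walk and are not tied to the drugs. At V9 there is also a small gap in the caffeine restriction.

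The size is unknown. The 6% and 22% illustrations rest on an assumed order effect and on the order varying at random at each visit; the range runs down to nothing where practice is stable. An effect on FMD or stiffness readings is a risk that the protocol leaves open, not one that it demonstrates. This is a cheap improvement worth making, not a threat to validity.

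**What to change.** In section 12.1.5, replace the free order for V3 and V9 with one fixed sequence, the same at both visits and both sites: arterial haemodynamics first, then post-ischaemia FMD, then GTN dilatation, and only afterwards post-bronchodilator spirometry and the 6-minute walk. Check this against the Trial Procedures Manual and make the two agree.

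In section 12.8.1, extend the caffeine restriction at V9 to the end of the vascular tests. V3 needs no change.

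The cost is one sentence in each section and less freedom to schedule within the visit. No procedure or visit is added.
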